#### Secondary outcome measures

Data on secondary outcome measures will be gathered by means of self-administered questionnaires such as, NEA [18], EQ-5D-5 L [41], SF-36[42], TIC-P [43] and PRODISQ[44].

##### - Sustainable employability

After commencing a treatment intervention, a follow-up measurement will take place at 12 and 18 months to analyze the sustainability of employability. An intervention will be deemed to be unsuccessful when absenteeism of more than fourteen consecutive days after receiving the productivity intervention occurs. On the basis of previous research, it will be assumed that the long-term effect of the employability intervention stabilizes after 18 months [24].

##### - Self-rated health

Self-related health will be assessed using one item from the Short Form Health Survey (SF-36). This widely used measurement tool describes how a respondent values and assess his/her general health [46]. Data gathered via questions derived from the NEA [18] will be used to detect health complaints underlying work disability and co-morbidity.

##### - Quality of Life

An explorative analysis of productivity costs and quality of life showed a clear relationship between both variables [46]. Therefore, quality of life will be measured in work-disabled employees by using the EuroQoL five dimensions, five levels (EQ-5D-5 L) [41]. The EQ-5D-5 L comprises 5 dimensions: mobility, self-care, usual activities, pain/discomfort and anxiety/depression. There are five possible answers for each dimension, defining (5^5^) 3125 possible health states. Furthermore, the EQ-5D-5 L includes a visual analogue scale (VAS) rating from zero (worst imaginable health state) to 100 (best imaginable health state) [41].

### Economic evaluation

Self-reported questionnaires will capture the costs and benefits from a societal perspective, thus independently of those who bear the costs, and those who receive the benefits. Self-reported questionnaires appear to be a reliable alternative for cost-diaries, at least for a recall period of 6 months, since participants will still remember significant life events [45,47-49]. Costs that arise in different years will be discounted at 4% [50]. Costs directly related to the provision of the employability intervention will be objectively registered via the providers of the employability intervention. Direct healthcare costs and direct non-healthcare costs comprise respectively: costs of visits for primary and secondary care, home care, drugs, and for visits to an alternative or informal health therapist. Direct costs will be measured by an adapted version of the Trimbos/iMTA questionnaire for costs associated with psychiatric illness [43] and will be estimated on the basis of prices suggested in the cost calculation guidelines for healthcare in the Netherlands [50]. The prices of prescribed drugs will be based on Daily Defined Dosage (DDD) taken from the Royal Dutch Society for Pharmacy [50]. Indirect costs will be determined by measuring data on the costs of lost productivity due to work disability and are derived through the PRODISQ [46]. The indirect costs of production loss due to sick leave will be calculated by means of the friction cost method whereby the number of days of sickness absence and lost earnings are used to calculate the costs of production losses. Lost earnings will be determined on the basis of the differences between income at baseline and income at follow-up. Based on a mean added value of the Dutch working population, production losses are confined to the period needed to replace a sick employee [44]. The indirect costs of productivity losses without sick leave will be based on the number of days in which productivity was hindered due to health complaints and an estimation of the efficiency in these days [51]. Furthermore, compensation will be taken into account when determining production loss. Information about the number of hours to catch up with the work will be obtained as well as the way in which this compensation was achieved. If these data are considered invalid, for example because the income data of too many employees are unknown, we will use national data of average production value per worker, related to the education level and labour sector.

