#### Usual work resumption care in the Netherlands

The Gatekeeper Improvement Act stipulates that the responsibility for work resumption lies with the employer and the employee. The employer is obliged to start an employee's work resumption programme as quickly as possible, so the employee can resume his/her own work or other adequate work. In return, the employee should accept the work activities the employer provides. Furthermore, and unique in the world, the Dutch reintegration process provides the employer with salary and mandatory reintegration obligations for a period of two years [36]. Participants included in the care as usual group will continue to receive care for their health complaints, but attention to work-related factors influencing these will only occur minimally. Nevertheless, since attention to labour and health-related characteristics is obligatory under the Gatekeeper Improvement Act [36], participants in the care as usual group who are work-disabled will also receive adequate care (care as usual). Participants included in the control group will be treated and supervised according to good clinical practice based on the evidence-based guidelines of the Dutch association of occupational physicians [37,38].

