#### Participants

Employees eligible for participation in the study will be work-disabled or at risk of work disability due to medical restrictions. In order to identify these employees, we will use employer registration forms, registrations with health care organizations and insurance companies, and registration forms from those providing the intervention. Employees eligible for inclusion will be 18 to 63 years of age, perform paid labour for at least 12 h per week, and are able to communicate in Dutch. Reasons for exclusion are absenteeism for 1.5 years or longer, fulltime students with a student job, informal caregivers and/or volunteers.

In order to recruit a sufficient number of eligible employees, one or more health care providers providing an employability intervention will screen service users for inclusion in the study. When appropriate, information on the research will be provided to the patient. This will be done orally by the health care provider, possibly supported by a handout containing contact information for the researchers, what is expected of participants, privacy concerns, and so on. A self-completion card will be attached to each flyer (handout) consisting of a short checklist for inclusion and informed consent form for signing. The employee is requested to fill in the short checklist, sign the informed consent form, and send these back to the researcher. Participants will have at least 1 week to consider their participation in the study before signing the informed consent form. Participants will be screened for exclusion by the researcher on the basis of answers provided on the checklist. If an employee meets all the selection criteria and is willing to sign the consent form, randomization or matching will then place. Before the intervention starts, the first (baseline) measurement occurs. An email with a login code is sent to all participants, and they will be asked to fill in the baseline questionnaire. The questionnaire for the intervention group is identical to the one for the control group.

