#### Timeline of the study

During recruitment, employees will be asked whether they want to participate in the research by one or more health care providers operating in the employability intervention. Participation requires employees to fill in a self-reported online questionnaire at time points T0 (baseline), T1 (6 months after admission), FU1 (12 month follow-up) and FU2 (18 month follow-up). After 18 months the study results for sustainable employability and quality of life are expected to extend into subsequent years. The timeline of the study can also be found in Figure 2.

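### The societal cost of sick leave takes the change in the employee's income as an input, and this does not measure lost output while the employer is obliged to pay salary

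*Protocol article*

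**What the plan says.** The costing section (Economic evaluation, before Sample size) takes a societal perspective, "thus independently of those who bear the costs, and those who receive the benefits". For sick leave it names the friction cost method, in which "the number of days of sickness absence and lost earnings are used to calculate the costs of production losses". It then defines the earnings term: "Lost earnings will be determined on the basis of the differences between income at baseline and income at follow-up".

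The next sentence limits losses to the time needed to replace the employee and refers to a mean added value of the Dutch working population. It does not say whether that value is the price of an absent day or how it relates to the income term. If the data are judged invalid, with too many unknown incomes as the example, "we will use national data of average production value per worker, related to the education level and labour sector".

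Two other sections bear on this:

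- Usual work resumption care in the Netherlands: "the Dutch reintegration process provides the employer with salary and mandatory reintegration obligations for a period of two years". The share of salary paid is not given.
- Participants: "Employees eligible for participation in the study will be work-disabled or at risk of work disability due to medical restrictions". Entry is open to people already on sick leave: "Reasons for exclusion are absenteeism for 1.5 years or longer".

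**The concern.** From a societal perspective, the cost of an absence is the output not produced, whoever pays for it. While the employer goes on paying, the employee's income hardly registers that loss. An income difference is an employee-perspective quantity, and here it is entered in a societal account.

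The reference point adds a second problem. For participants already absent at T0, baseline income may already be sick pay. Any fall in income is then built into the reference, and a later return to full pay appears as a negative loss.

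The abstract names two cost components, healthcare and lost production, and all the interventions aim to reduce absence. If days saved carry little or no money value, the cost side of the ICER and ICUR is distorted, and so are the acceptability curves, for every intervention evaluated under this shared design.

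**Working it through.** The protocol gives no wage, production value, salary share or friction period, so there is no figure of its own to reproduce. The rule can still be followed through in relative terms.

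**Inputs from the article.** Lost earnings are income at baseline minus income at follow-up. The salary obligation lasts 24 months. Absence at entry is below 18 months. Measurements are at "T0 (baseline), T1 (6 months after admission), FU1 (12 month follow-up) and FU2 (18 month follow-up").

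**Assumption.** c is the share of salary continued during sick leave, shown from 0.7 to 1.0 because the article does not state it.

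**Price of an absent day.** Let W be the full wage for a day, and Y0 and Y1 the income per day at baseline and follow-up. If the income difference is the daily price, then price / W = (Y0 − Y1) / W.

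| Situation | Formula | c = 1.0 | c = 0.9 | c = 0.8 | c = 0.7 |
|---|---|---|---|---|---|
| At work at T0, absent at follow-up | 1 − c | 0% | 10% | 20% | 30% |
| Absent at both, pay unchanged | c − c | 0% | 0% | 0% | 0% |
| Absent on reduced pay at T0, recovered at follow-up | c − 1 | 0% | −10% | −20% | −30% |

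The negative price in the last row would apply to the days of absence that came before the return. If the income term is instead a separate component added to the days, the same negative amount enters as a saving.

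Under the plan's own fallback, a fully absent day inside the friction period costs 100% of the production value in all three situations, before compensation.

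**Reach of the salary obligation.** With a months of absence at entry, the covered part of follow-up is min(18, 24 − a) months:

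- a = 0 or 6: 18 of 18 months.
- a = 12: 24 − 12 = 12 of 18 months.
- a just under 18: about 24 − 18 = 6 of 18 months.

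If absence at entry were spread evenly over 0 to 18 months (an assumption), mean coverage is (6 × 18 + 12 × 12) / 18 = 14 months, since 24 − a averages 12 for a from 6 to 18. That is 14 / 18 = 78% of follow-up.

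**Does the fallback catch this?** Its stated example is missing income. Complete and accurate income data would not set it off, yet those are the data that give the values in the table. No threshold is set for how many unknown incomes are too many, so the choice of price could be made after the data are seen.

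**The case against.** The strongest reply is that the costing text can be read in more than one way. Days of absence are an explicit input, and how days and earnings combine is not stated. The mean added value in the following sentence may be meant as the price of a day in the friction period; on that reading an absent day is not priced near zero. This stands as a limit: the table holds only if the income difference is the daily price. It does not clear the plan, because on the other reading two prices apply to one quantity and the text does not choose between them.

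Other replies stand in part:

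- The salary share is not in the article, and the obligation can end during follow-up for people absent more than 6 months at entry. Both affect the size of the error.
- The friction cap limits how many days count. It does not change the price per day.
- Missing income is only an example of invalid data, and sensitivity analyses are planned. Neither guarantees that the income rule is replaced.
- Employees who are only at risk may be at work at T0, so the contaminated baseline concerns some participants, in a proportion not given.
- This is a condensed article that refers to cited costing sources. The point, however, is a rule that the article states, not a detail that it leaves out.

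A reader might infer that the rule removes most of the cost difference between groups, or that 70 to 100% of all absence cost is lost. The documents do not support either. No between-group calculation is possible from them, the lower figure rests on an assumed 70% salary share, and a comparison with the full wage over a long absence ignores the friction cap.

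**Conclusion.** The point holds in a limited form. Income change is not a measure of lost output under the salary obligation that the article itself describes, and it conflicts with the stated societal perspective. Read as the daily price, it values an absent day at 0% of the wage under full or unchanged pay, at up to 30% if at least 70% is continued (assumed) and the person was at work at T0, and below zero after recovery from reduced pay. The role of the mean added value is left unclear, and the fallback would not be set off by good income data.

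The bias affects absence costs only. Healthcare costs, intervention costs and productivity loss while at work are costed separately, and the primary outcome is untouched. The error passes into the ICER, the ICUR and the acceptability curves. Its size there, in euros or between groups, cannot be derived from the article.

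**What to change.** Remove the income-difference rule from the societal base case. Price absence days within the friction period, net of compensation, at the national average production value by education level and labour sector, which makes the plan's present fallback the primary rule. State that this is the single price, and either drop the mean-added-value phrase or reconcile it with that price. Report income change only in an employee-perspective table, a perspective that the Discussion already foresees.

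The cost is a change of text. Days of absence and catch-up hours are already to be collected. The downside is that individual wage variation is replaced by group averages.

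It would be tempting also to start the friction period at the first day of each spell, before T0. That is not part of this fix: the article does not say that start dates of earlier spells are collected, and the step could set follow-up loss to zero for people who enter after a long absence.

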
### Sample size

For the economic evaluation of the three newly developed employability interventions, the study sample size was pre-specified by the researchers and the developers of the particular interventions. For the sample size calculation of the existing 'Best Practices', we expect that a Hazard Ratio (HR) of 2.0 indicates a relevant difference in the average number of hours/days of lost work due to work disability between employees in the intervention group and employees in the control group after 18 months. This HR is based on findings of recent studies in occupational health care [25,52-55]. With a power of 80% at a 0.05 significance level, the sample size was calculated to be 120 employees [56]. Taking into account a dropout rate of 15%, 5% per follow-up measurement time, a total of 142 participants are needed. A dropout is defined as an employee who has not filled in the questionnaire at one or more measurement time-points.

### Data analyses

#### Effectiveness

All statistical analyses, performed to distinguish differences between the control group and the intervention group, will be performed according to the intention-to-treat principle. This means that the participants will remain in the group they were allocated to at baseline. All data regarding primary and secondary outcomes will be analysed using descriptive statistics. To control for protocol deviations likely to cause bias, data will be analyzed using per-protocol analyses whereby outcomes will be compared between those participants who received at least one or a partial intervention session and the control group. With the aim of correcting for possible regression to the mean, the baseline value of the particular outcome variable will be added to the model. Days of sick leave in the year before the inclusion, measured at baseline, will be added as a potential effect-modifier.

Diagnosis and prognostic parameters can be confounders, thus the Cox regression analysis for confounders will be used to adjust for differences between control and intervention groups. If necessary, differences in baseline will be adjusted for prognostic dissimilarities. Missing data will be handled using SPSS missing value analysis on item level. Completely missing measurements will be handled using multiple imputation.

The primary dependent variable is days of absence from work. In order to estimate the number of absence days, survival analyses will be used. There are two reasons why we opted to use survival statistics. Firstly, the time to sustainable employability is unlikely to be normally distributed which will make parametric statistical analysis difficult or inappropriate. Increasing productivity can occur quite early, possibly within months, but can also, as expected in the care as usual situation, may not be prolonged or may even decrease again. Secondly, survival analysis accounts for dropout by the technique of censoring. Participants who drop out will have the same hazard of sustainable employment than those that remained in the study. The Cox Proportional hazard model will therefore be used to analyse the HR of the days of sick leave duration. Reduced sickness absence duration in calendar days will be analysed with the Kaplan Meier survival method, and the differences in absence duration between both groups will be tested with a log rank test.

To analyse the secondary outcomes, longitudinal multilevel analyses will be used to assess the differences in health and quality of life between the control group and the intervention group.

Data will be analysed in SPSS 17.0.

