#### Randomization/matching

In the case of randomization, the minimization method will be applied. Minimization aims to ensure an excellent balance for several prognostic factors in small groups [40]. Employees consenting to participate will be pre-stratified according to age (18-32 years, 33-48 years, 49-64 years), gender, and working hours (12-24 h/week, > 24 h/week). Since health care providers will treat participants in both the intervention and in the control groups, the study cannot be blinded. Matching i.e. formulating experimental and control groups on the basis of pairing participants on the basis of predetermined matching criteria will be used. These matched-criteria are age, working hours and health complaints. Thus, an employee in the intervention group will be matched to someone meeting the same criteria who will then act as a member of the control group.

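### The per-protocol comparison and the 14-day failure rule both hang on receiving the intervention, so two supporting or secondary results do not treat the arms alike

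*Protocol article*

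**What the plan says.** Under Data analyses, Effectiveness, the protocol article puts all between-group analyses under intention-to-treat: "This means that the participants will remain in the group they were allocated to at baseline". It then adds a second comparison with a stated purpose: "To control for protocol deviations likely to cause bias, data will be analyzed using per-protocol analyses". The set is defined so that "outcomes will be compared between those participants who received at least one or a partial intervention session and the control group". No criterion is set for controls.

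Under Randomization/matching, the quasi-experiments form pairs: "an employee in the intervention group will be matched to someone meeting the same criteria who will then act as a member of the control". The same section states: "Since health care providers will treat participants in both the intervention and in the control groups, the study cannot be blinded".

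Under Secondary outcome measures, Sustainable employability, "a follow-up measurement will take place at 12 and 18 months to analyze the sustainability of employability". Failure is then defined: "An intervention will be deemed to be unsuccessful when absenteeism of more than fourteen consecutive days after receiving the productivity intervention occurs". No start point is given for care as usual.

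**The concern.** Both rules use an event that only one arm has.

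**Per-protocol set.** Whether an employee attends a first session is decided after allocation and may be related to prognosis. Controls who would not have attended cannot be identified and stay in. The remaining intervention employees are therefore a selected group compared with an unselected one. The set also misses the deviations it is meant to handle. One partial session qualifies, so partial adherers remain. Controls who pick up intervention content are kept, although the same providers treat both groups. In a matched design, dropping an employee and keeping the partner undoes the pairing.

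**14-day rule.** If the clock starts at receipt of the intervention, the analyst must invent a start for controls. Different choices give different results even when the true relapse risk is equal.

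At stake are a supporting effect estimate that could seem to confirm or contradict the main result, and a secondary outcome with no agreed comparison. The article says that its design will be applied to each included intervention, so both rules would be repeated.

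**Working it through.** **Scale.** The plan attaches no figure to either rule, so its sample size serves only to set the scale. 120 / (1 − 0.15) = 141.2, rounded up to 142, as stated. For a hazard ratio of 2.0 ("we expect that a Hazard Ratio (HR) of 2.0 indicates a relevant difference"), two-sided 0.05 and 80% power, Schoenfeld gives 4 × (1.96 + 0.842)² / (ln 2)² = 65.3, so 66 events; Freedman gives (3/1)² × (1.96 + 0.842)² = 70.6, so 71. Among 120 employees that is 55–59% with the event. The share is not stated; I take 57%, and 43% as a lower alternative.

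**Per-protocol bias with no true effect.** Assumed, because the article gives neither: a share q of employees would not start, and they return at r times the starters' rate λ. Times are exponential and censored at 18 months.

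- Intervention arm after exclusion: hazard λ.
- Controls, still a mixture: hazard λ × [(1 − q)e^(−λt) + q·r·e^(−rλt)] / [(1 − q)e^(−λt) + q·e^(−rλt)].
- At time 0 the hazard ratio is 1 / [(1 − q) + q·r]. For q = 0.20, r = 1/3: 1 / (0.80 + 0.067) = 1.15.
- At 18 months, with 57% returned overall, 36% of starters and 71% of non-starters are still absent. Non-starters are then 0.2 × 0.71 / (0.8 × 0.36 + 0.2 × 0.71) = 33% of the controls still absent, and the ratio is 1 / (0.67 + 0.33/3) = 1.28.
- The Cox estimate averages over follow-up and comes to 1.20.

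Large-sample Cox values, from solving the expected score equation (a range shows 43% to 57% with the event):

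| Non-starters | r = 1/3 | r = 1/2 | r = 1 | r = 2 |
|---|---|---|---|---|
| 5% | 1.04 | 1.03 | 1.00 | 0.96–0.97 |
| 10% | 1.09 | 1.06 | 1.00 | 0.92–0.93 |
| 20% | 1.18–1.20 | 1.13 | 1.00 | 0.86–0.87 |

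Simulated data sets agree within about 0.02 (for r = 1/3: 1.03, 1.09 and 1.18 in one set of runs). With everyone kept, the simulated hazard ratio is 0.99–1.01.

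False-positive rate: shift = ln(HR) × √events / 2, with 120 × 0.57 = 68 events. For HR 1.20 the shift is 0.76, and Φ(0.76 − 1.96) + Φ(−0.76 − 1.96) = 12%. At 43% with the event it is about 9%. For 5% non-starters it stays near 5%.

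**14-day rule.** Assume the same constant relapse hazard in both arms, controls counted from baseline and the intervention arm from month m. If the 18-month risk in controls is p, the intervention arm shows 1 − (1 − p)^((18 − m)/18).

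| p | m = 1 | m = 3 | m = 6 |
|---|---|---|---|
| 20% | 19% | 17% | 14% |
| 40% | 38% | 35% | 29% |
| 60% | 58% | 53% | 46% |

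For p = 40% and m = 6: 1 − 0.6^(12/18) = 0.289. An apparent gain of 11 percentage points arises from the clock alone. With one start point for both arms the risks are equal.

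**The case against.** The strongest reply is that little depends on either rule. Intention-to-treat governs the effect analysis and, under Economic evaluation, the cost analysis. The attendance threshold is so low that only complete non-starters leave, which keeps the set close to intention-to-treat. With few non-starters, or equal prognosis, the bias is negligible. All of this stands, and it limits the point to supporting and secondary results.

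Four stronger readings are tempting, and the article does not support them.

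- *Controls can never fail the 14-day rule.* That is over-literal. The questionnaire is identical in both arms, sustainability is measured at 12 and 18 months, and Study design once calls the comparator a conventional intervention. What is shown is a missing start point for controls.
- *The 14-day rule defines the event in the main survival analysis.* Time to sustainable employability appears there only as a reason for choosing survival methods. The dependent variable is named as days of absence, and Cox and Kaplan-Meier are applied to sick-leave duration.
- *The per-protocol rule costs a large part of the power.* If early returners are dropped before a first session at 2 months, simulated power at a true hazard ratio of 2.0 falls from 79% to about 53%. That assumes a doubled return rate before any session has been given. If the effect starts at the first session, intention-to-treat itself has 68% against 52%; with a first session at 2 weeks, 76% against 73%. These timings are not in the article, and power is a weak yardstick for a supporting analysis.
- *The bias favours the intervention.* It can go either way.

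**Conclusion.** The point holds for two results. The per-protocol comparison selects on behaviour after allocation in one arm and cannot do what the article says it is for. Under the assumed 5–20% of non-starters and no true effect, the hazard ratio moves to about 1.03–1.20 if they return slowly, to 0.97–0.86 if they return fast, and not at all if their prognosis equals that of starters. All these inputs are assumptions; the direction in any given trial is unknown. The sustainable-employability outcome lacks a start point in the usual-care arm, so it cannot be compared between arms as written. The main intention-to-treat analyses are untouched. It should be corrected, but it does not threaten the primary result.

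**What to change.** **Per-protocol analysis.**
- Delete the claim that it controls bias, and label it supportive.
- In matched designs, exclude both members of a pair when the intervention member did not start. This keeps the balance on the matching criteria. It does not remove selection on unmeasured prognosis, which is why the label matters.
- In randomised trials, use an adherence-adjusted estimate with allocation as the instrument, where providers' records show who started. The article mentions provider registration only for intervention costs, so first confirm that attendance is recorded. If it is not, rely on intention-to-treat.

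**14-day outcome.** Count it in both arms over the same window fixed from allocation, for example any absence of more than 14 consecutive days between the 6- or 12-month and the 18-month measurement. In quasi-experiments, the baseline date can stand in for allocation. Starting the clock at first return to work is less suitable: the trials enrol at-risk employees who may never have been absent, and earlier returners would be exposed to relapse for longer. A fixed window works for them and for employees still in their initial absence.

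**Cost.** One reworded secondary outcome and one changed supporting analysis. The sample size and the main analysis stay as they are.
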